## Introduction

1

Autism is a neurodevelopmental condition characterized by two core diagnostic features, as defined by the Diagnostic and Statistical Manual of Mental Disorders (DSM-5): i) persistent deficits in social communication and interaction, manifesting as impairments in emotional reciprocity, verbal and nonverbal communication, and developing and maintaining relationships; and ii) restricted, repetitive patterns of behavior, interests, or activities, alongside cognitive inflexibility (1). These symptoms typically emerge in early childhood and cause significant functional impairment across social, occupational, and educational domains (2). In Ecuador, the estimated prevalence of autism is 682.70 cases per 100,000 individuals (3).

Although behavioral and cognitive impairments dominate autistic symptomatology, concomitant conditions such as malnutrition are prevalent. For example, studies indicate that overweight affects up to 35% and undernutrition up 20% of autistic children (3). Furthermore, autistic individuals are at higher risk of malnutrition, whether underweight, overweight, or obese, compared to non-autistic (NA) peers (4, 5). A critical driver of these disparities is sensorimotor integration differences (SMD), which alters responses to sensory stimuli (e.g., tactile, auditory, gustatory) in 69–95% of autistic individuals (6, 7).

Beyond food-related sensitivities (e.g., aversion to specific smells, tastes, textures), SMD contributes to malnutrition by underpinning core autistic traits including stereotypical behaviors, reduced behavioral flexibility, hyper- or hypo-reactivity, and anxiety. These traits lead to feeding problems such as food neophobia, heightened food selectivity, pica, and rumination (8). Consequently, individuals may suffer from deficiencies in essential nutrients like protein, iron, and vitamins, while consuming excessive amounts of polyunsaturated fats compared to their NA peers (8, 9). Such nutritional imbalances can further worsen core autistic symptoms and increase the risk of chronic conditions later in life (3, 10).

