A major limitation in understanding the SMD-nutrition-microbiota relationship has been the reliance on caregiver-reported SMD assessments, such as the Short Sensory Profile (SSP). While instruments like the SSP have been extensively used in autism research, they remain subjective measures that may be influenced by caregiver perception, cultural context, and socioeconomic factors (17, 18). Moreover, their performance in non-Western populations has not been thoroughly evaluated. Neurometric tools such as pre-pulse inhibition of the startle response (PPI), offer an objective alternative for measuring sensorimotor assessment in autistic cohorts (19, 20). Innovations, such as a smartphone-based tool that enables accessible, non-invasive at-home neurobehavioral assessments, can provide standardized tests for measuring sensory gating and adaptation through the assessment of PPI and startle habituation (SH), as well as general sensorimotor behaviors (21, 22).

Therefore, we hypothesize that SMD in autistic children is associated with imbalanced dietary patterns, leading to malnutrition and changes in GM diversity and composition. These physiological alterations may collectively exacerbate autistic symptom severity, which in turn could further intensify SMD and feeding difficulties, establishing a self-perpetuating cycle of worsening symptoms and malnutrition. Our main objective is to investigate the relationships between SMD, dietary patterns, nutritional status and GM characteristics in autistic children compared to NA peers. Specifically, the study will (1): Compare dietary patterns and nutritional status between autistic children and NA peers (2). Assess differences in the GM (diversity, composition) between autistic children and NA peers (3). Quantify SMD by assessing PPI and SH and compare profiles across autistic children and NA peers (4). Examine associations between SMD, dietary patterns, nutritional status, GM profiles, and autistic symptom severity (5). Explore whether SMD mediates the relationship between autism and adverse nutritional/GM outcomes.

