#### Group C - non-autistic children with other neurodevelopmental disorders

2.2.3

This group will include children and adolescents aged 3 to 17 years (n = 100) diagnosed with intellectual, psychological, emotional, or behavioral developmental disorders not including autism.

*Inclusion criteria*

Age between 3 and 17 years.Diagnosis with psychological developmental disorders (ICD-10 F80-F89), which includes: F80 (specific developmental disorders of speech and language), F81 (specific developmental disorders of school skills), F82 (specific developmental disorder of motor function), F83 (mixed specific developmental disorders), F88 (other disorders of psychological development) and F89 (unspecified disorder of psychological development). Diagnosis with intellectual disabilities (ICD-10 F70-F79), including F70 (mild mental retardation), F71 (moderate mental retardation), F78 (other mental retardation), F79 (unspecified mental retardation). Diagnosis with emotional and behavioral disorders usually occurring in childhood and adolescence (ICD-10 F90-F98), which includes F90 (hyperkinetic disorders), F91 (conduct disorders), F92 (mixed disorders of conduct and emotions), F93 (emotional disorders with onset specific to childhood), F94 (disorders of social functioning with onset specific to childhood), F95 (tic disorders), and F98 (other emotional and behavioral disorders that commonly occur in childhood and adolescence).

*Exclusion criteria*

AQ-10 score of 6 points or higher.POSI score of 3 points or higher.Diagnosis with or report of having received therapy or treatment for a neurodevelopmental disorder coded as ICD-10 F84.Being unable to sit and/or stand autonomously.

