#### Sample size

2.2.4

The sample size was determined based on the expected difference in malnutrition prevalence between autistic children and their NA peers in a cross-sectional comparison. According to the *Encuesta Nacional de Salud y Nutrición* (24), 35% of the Ecuadorian children younger than 11 years of age are overweight or obese, while among adolescents the prevalence of overweight or obesity is 30%. The prevalence of extreme thinness is 2% among Ecuadorian children and adolescents. Based on these figures, we assumed an approximate malnutrition prevalence of 37% in the NA population.

There is no published data on prevalence of malnutrition in Ecuadorian autistic children up to date. To estimate this value, we referred to data from a recent study in another Latin American country (Mexico), which reported a malnutrition prevalence of 57.50% among autistic children (45% obese/overweight, and 12.50% underweight) (25). To estimate the sample size required to detect this difference (~20.50%) between the groups, we used the formula for comparing two independent proportions in a two-sided hypothesis test (26):

$n=\frac{{\left(Z_{\alpha /2}+Z_{\beta }\right)}^{2}\times [p_{1}(1-p_{1})+p_{2}(1-p_{2})]}{{\left(p_{1}-p_{2}\right)}^{2}}$, where:

$Z_{\alpha /2}$ = 1.96 (corresponding to a 95% confidence level),

$Z_{\beta }$ = 0.84 (corresponding to 80% power),

$p_{1}$ = 0.57 (estimated malnutrition prevalence in autistic children - Group A),

$p_{2}$ = 0.37 (estimated malnutrition prevalence in NA children - Group B).

The formula yields an approximate sample size of 94 participants per group. To account for a projected non-response rate of 5%, the sample size increases to 100 participants per group. This sample size is also adequate for detecting large effect sizes in secondary comparisons, such as the prevalence of SMD, which has been reported to be between 81.50% and 95.00% among autistic children and may reach 16.50% in children of the population (7, 18, 27). Thus, our sample will be sufficient for the validation of the neurometric test, achieving a statistical power close to 1.

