### “Proyecto Wiñay” in the current Ecuadorian context

4.1

Feeding challenges in autistic individuals pose significant health concerns, particularly due to their impact on nutritional status (67, 68). SMD constitutes a key contributor to these challenges, yet its association with dietary patterns and GM characteristics remains unexplored in the Ecuadorian pediatric population. Our study aims to fill this gap by conducting an integrated assessment of SMD, dietary patterns, and GM characteristics in autistic children from the Andes, a group known to face high malnutrition rates and limited healthcare access (24). While other studies acknowledge the link between SMD and malnutrition in autism, our approach is distinct in its specific adaptation of methodologies to the Ecuadorian context. We hypothesize that SMD contributes to restrictive diets that subsequently alter GM composition and diversity, potentially exacerbating core autistic symptoms and perpetuating a cycle of malnutrition.

This research employs innovative techniques, including neurometrics to objectively assess SMD through measures of sensory gating and habituation as well as general motor behaviors. Additionally, GM characteristics will be evaluated in a population with high prevalence of intestinal parasitosis, a factor often overlooked in studies from high-income countries (69). Further, we will use WHO-standardized anthropometric measurements to assess three groups: autistic children, NA children, and children with developmental disorders other than autism. This comparative approach will provide valuable insights into the unique nutritional challenges and GM alterations specifically associated with autism.

Unlike previous Ecuadorian studies (e.g., Zurita et al., 2020), which focused primarily on nutritional status and GM, “Proyecto Wiñay” offers a more comprehensive approach by incorporating objective SMD analysis (70). Furthermore, our study will recruit a larger sample size from a more ethnically diverse population (including participants from both Quito and Riobamba cities) and across a broader age range. Although cross-sectional, our study has the potential to establish the basis for future longitudinal studies tracking GM changes or symptom severity linked to sensorimotor-mediated dietary patterns.

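### Group C admits the whole ICD-10 F98 category, so it may include children enrolled solely for a feeding disorder or pica, which could bias the Group A versus C contrast and the pooled contrast toward the null

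*Protocol article*

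**What the plan says.** Section 2.2.3 describes Group C as follows: "This group will include children and adolescents aged 3 to 17 years (n = 100) diagnosed with intellectual, psychological, emotional, or behavioral developmental disorders". The qualifying diagnoses are listed as three-character ICD-10 categories, and the last is "F98 (other emotional and behavioral disorders that commonly occur in childhood and adolescence". No sub-code is singled out or removed. There are four exclusions: the AQ-10 cut-off, the POSI cut-off, inability to sit or stand, and "Diagnosis with or report of having received therapy or treatment for a neurodevelopmental disorder coded as ICD-10 F84". F84 is the only diagnosis excluded.

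The Introduction describes how sensorimotor differences and autistic traits are thought to produce malnutrition: "These traits lead to feeding problems such as food neophobia, heightened food selectivity, pica, and rumination". The first specific aim is to "Compare dietary patterns and nutritional status between autistic children and NA peers". The abstract counts Group C as 100 of the 200 non-autistic peers. Section 4.1 says the three-group comparison will give insight into the "unique nutritional challenges and GM alterations specifically associated with autism".

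In section 2.2.4 the sample size rests on Group A against Group B. The sponsor writes that "we assumed an approximate malnutrition prevalence of 37% in the NA population" and labels that rate as Group B's.

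**The concern.** Group C is the only group that can separate what belongs to autism from what belongs to neurodevelopmental disorder in general. For that, its children should not be chosen for the characteristic being compared. In the ICD-10 list, F98 is a residual category that includes feeding disorder of infancy and childhood with rumination (F98.2) and pica (F98.3). The article does not print that list, but anyone applying section 2.2.3 has to use it, so the sponsor can confirm the content directly.

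If that reading of F98 is right, a child whose only diagnosis is pica or a feeding disorder qualifies for Group C, and none of the four exclusions stops this. Group A enters on a diagnosis of autism, so the selection is one-sided. If such children have more disturbed diets, nutrition or microbiota than the rest of Group C, the differences between A and C shrink. The study would then lean toward finding that these problems are not specific to autism. Because Group C is half of the non-autistic peers, a diluted form of the same bias reaches any A versus B+C comparison.

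The named covariates (age, sex, socioeconomic status, medication use) do not address selection on eating behaviour. Adjusting for diet would remove part of what is being compared.

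**Working it through.** **Inputs from the article (section 2.2.4).** p1 = 0.57 for Group A; p2 = 0.37 for Group B; z-values 1.96 and 0.84; 94 per group before a 5% non-response allowance.

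**The plan's own figure.** n = (1.96 + 0.84)² × [0.57 × 0.43 + 0.37 × 0.63] / 0.20² = 7.84 × 0.4782 / 0.04 = 93.7, so 94 per group. This reproduces the stated number. 94 / 0.95 = 98.9, so 99, against the stated 100, which is close enough. With the same unpooled variance, 94 per group gives a standard error of √(0.4782 / 94) = 0.0713, and power Φ(0.20 / 0.0713 − 1.96) = 80.1%.

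**Assumptions the article does not supply.** Let f be the share of Group C whose only qualifying diagnosis is a feeding disorder or pica, and q their malnutrition prevalence. The rest of Group C is taken at 37%, which the article states for Group B and not for Group C.

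**Effect on A versus C.**
- Group C prevalence: pC = (1 − f) × 0.37 + f × q
- Difference: 0.57 − pC = 0.20 − f × (q − 0.37)
- Power: Φ[(0.57 − pC) / √((0.57 × 0.43 + pC(1 − pC)) / 94) − 1.96]

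Worked case, f = 10% and q = 0.57: pC = 0.9 × 0.37 + 0.1 × 0.57 = 0.390; difference 0.180; standard error 0.0717; power Φ(2.511 − 1.96) = 70.9%.

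| f | q | pC | A–C difference | Power, 94 per group |
|---|---|---|---|---|
| 0 | any | 0.370 | 20.0 points | 80.1% |
| any | 0.37 | 0.370 | 20.0 points | 80.1% |
| 5% | 0.57 | 0.380 | 19.0 points | 75.7% |
| 5% | 0.80 | 0.3915 | 17.9 points | 70.2% |
| 10% | 0.45 | 0.378 | 19.2 points | 76.6% |
| 10% | 0.57 | 0.390 | 18.0 points | 70.9% |
| 10% | 0.80 | 0.413 | 15.7 points | 58.7% |
| 20% | 0.57 | 0.410 | 16.0 points | 60.4% |

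**Effect on A versus B+C.** With B and C of equal size, the difference shrinks by half as much, f × (q − 0.37) / 2. With 94 against 188 and the same formula, power is 89.7% at f = 0. At f = 10% it is 88.4%, 86.4% and 81.8% for q = 0.45, 0.57 and 0.80.

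**Effect on A versus B.** None. Group C does not enter it.

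The article gives no figures for an equivalent calculation on dietary patterns or microbiota.

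**The case against.** **The content of F98 is not in the article.** True: neither sub-code appears there, and nothing says that pica or feeding disorder belongs to F98. But ICD-10 is the language in which the criterion is written, so its code list defines the criterion. It should be confirmed, which is quick.

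**Nothing shows that such children will enrol.** This stands. Group C spans 17 listed categories, and section 2.3 names a special education school, a neurodevelopment centre, educational institutions, social networks and parents' associations, but no feeding or nutrition clinic. The share f may be small or zero. A reader might infer that part of Group C is in fact selected on the outcome and that the contrast is in fact pulled toward zero. The text only permits that enrolment.

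**A feeding disorder is not the sized outcome.** This also stands. Malnutrition in section 2.2.4 runs in both directions: overweight or obesity supplies 35 of the 37 points and thinness 2. A feeding disorder or pica is a cause or correlate of malnutrition. The bias runs toward the null only if q exceeds 0.37. The concern is more direct for dietary patterns, where selection is on eating behaviour itself, but that cannot be quantified.

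**The 80% power belongs to A versus B.** Correct. The article claims no power for malnutrition in A versus C, so the figures above show sensitivity and do not contradict a stated claim. It would be wrong to say that every comparison with non-autistic peers is affected.

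**A broad comparator is legitimate, and sensitivity analyses are promised.** A broad Group C is a fair choice. However, section 4.2 describes its sensitivity analyses in terms of modelling assumptions and medication, and the stated limitations do not mention this selection. Eligibility is fixed in the article and is harder to repair after recruitment.

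**Conclusion.** The eligibility gap is real, and its consequence is conditional. As written, section 2.2.3 would accept a child into Group C solely for a feeding disorder or pica, provided F98 covers these as the ICD-10 list is understood to. The Introduction treats those same problems as steps toward the outcomes. The selection is one-sided, and the named covariates cannot correct it. It could attenuate A versus C and, at half the strength, A versus B+C, for diet, nutritional status and microbiota.

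The size cannot be derived from the article. At f = 10% the A–C malnutrition difference loses 0.8, 2.0 or 4.3 of its 20 points for q of 0.45, 0.57 or 0.80, with power losses of 3.5, 9.2 and 21.4 points from 80.1%. With f = 0 or q = 0.37 nothing is lost. These figures assume f and q, and a 37% rate in the rest of Group C. The documents do not support a claim of established bias or of any minimum loss of power. Because the remedy is cheap at entry, the criterion should be amended.

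**What to change.** In section 2.2.3, state that a feeding disorder or pica (F98.2, F98.3, once confirmed against the ICD-10 list) cannot be the sole qualifying diagnosis for Group C. Keep children who also have another listed diagnosis, so that co-occurring feeding problems are handled as in Group A. Excluding every Group C child with a feeding problem while leaving Group A unrestricted would create the opposite bias.

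Record the F98 sub-code at entry, because the criteria now work at the three-character level and the article does not say that sub-codes are captured.

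If such children are already enrolled, flag them and leave them out of the Group C diet, nutritional-status and microbiota contrasts. Report the contrasts with them included as a sensitivity analysis.

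The cost is one line in the criteria, one extra recorded code, a slightly narrower Group C and a few candidates replaced at screening.

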#### Sample size

2.2.4

The sample size was determined based on the expected difference in malnutrition prevalence between autistic children and their NA peers in a cross-sectional comparison. According to the *Encuesta Nacional de Salud y Nutrición* (24), 35% of the Ecuadorian children younger than 11 years of age are overweight or obese, while among adolescents the prevalence of overweight or obesity is 30%. The prevalence of extreme thinness is 2% among Ecuadorian children and adolescents. Based on these figures, we assumed an approximate malnutrition prevalence of 37% in the NA population.

There is no published data on prevalence of malnutrition in Ecuadorian autistic children up to date. To estimate this value, we referred to data from a recent study in another Latin American country (Mexico), which reported a malnutrition prevalence of 57.50% among autistic children (45% obese/overweight, and 12.50% underweight) (25). To estimate the sample size required to detect this difference (~20.50%) between the groups, we used the formula for comparing two independent proportions in a two-sided hypothesis test (26):

$n=\frac{{\left(Z_{\alpha /2}+Z_{\beta }\right)}^{2}\times [p_{1}(1-p_{1})+p_{2}(1-p_{2})]}{{\left(p_{1}-p_{2}\right)}^{2}}$, where:

$Z_{\alpha /2}$ = 1.96 (corresponding to a 95% confidence level),

$Z_{\beta }$ = 0.84 (corresponding to 80% power),

$p_{1}$ = 0.57 (estimated malnutrition prevalence in autistic children - Group A),

$p_{2}$ = 0.37 (estimated malnutrition prevalence in NA children - Group B).

The formula yields an approximate sample size of 94 participants per group. To account for a projected non-response rate of 5%, the sample size increases to 100 participants per group. This sample size is also adequate for detecting large effect sizes in secondary comparisons, such as the prevalence of SMD, which has been reported to be between 81.50% and 95.00% among autistic children and may reach 16.50% in children of the population (7, 18, 27). Thus, our sample will be sufficient for the validation of the neurometric test, achieving a statistical power close to 1.

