## Abstract

**Background:**

Autistic children experience disproportionately high rates of malnutrition compared to non-autistic (NA) peers. Sensorimotor integration differences (SMD), prevalent in 69–95% of autistic individuals, are hypothesized to drive this disparity. SMD contributes to core autistic traits that exacerbate feeding difficulties (e.g., food selectivity), potentially leading to malnutrition and gut dysbiosis. Current caregiver-reported SMD assessments lack validity in autistic populations and are prone to cultural and socioeconomic biases, limiting insight into nutritional outcomes.

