##### Prepulse inhibition of acoustic startle response

3.5.4.1

PPI is the behavioral phenomenon whereby the magnitude of the startle response is inhibited when a short, loud startling sound (the pulse) is preceded by a weaker sound that does not itself elicit a startle reflex (the prepulse). The PPI training session will last approximately 12 minutes, contain 44 trials, and will be administered to all children. We will use a pulse consisting of a 105 dB, 50 ms white noise burst. The prepulse will consist of a 50 ms white noise burst of varying amplitude that is always softer than the pulse, delivered at three different intensities: 10% (soft), 25% (medium), and 40% (high) of the pulse amplitude. For the soft and high prepulse intensities, a fixed interstimulus interval (ISI) of 120 ms will be used between the prepulse and the pulse. For the medium prepulse intensity, ISIs of 60, 120, and 240 ms will be used. The session will begin with 2 practice trials containing white noise bursts at various soft intensities to allow the participant to relax and settle into the movie. Subsequently, 7 blocks of 6 trials will be presented. Each block will consist of one pulse-only trial and five prepulse-pulse trials. The order of trials will be randomized and will differ between blocks. The intertrial interval will be randomly set between 4 and 14 seconds.

*Dependent variables*

Acoustic startle response (ASR) amplitude and variability: The normalized peak eyelid closure amplitude in response to the pulse-alone trials and its standard deviation.ASR latency to peak: The time from pulse onset to the peak of the eyeblink response.Prepulse-elicited response amplitude: The normalized peak eyelid closure amplitude in response to the prepulse-alone.Prepulse-elicited response latency: The time from prepulse onset to the peak of the eyeblink response it elicits.Prepulse-pulse response amplitude and variability: The normalized peak eyelid closure amplitude in response to the pulse when it is preceded by a prepulse, and its standard deviation.Percent PPI: The percentage inhibition of the ASR amplitude due to the prepulse, calculated as: % PPI = 100 - [(mean ASR amplitude on prepulse-pulse trials)/(mean ASR amplitude on pulse-alone trials) × 100].Prepulse excitation: A measure of hyper-responsiveness to the prepulse itself.Habituation: The change in normalized ASR amplitude to pulse-alone trials over the course of the entire session.

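### The power close to 1 claimed for validating the neurometric test is the power of a prevalence contrast, not of a validation

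*Protocol article*

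**What the plan says.** Section 2.2.4 sizes the study on malnutrition prevalence, 0.57 against 0.37, and arrives at 94 per group, raised to 100 for 5% non-response. It then calls this sample adequate for large effects in secondary comparisons. The example is SMD prevalence, cited as 81.5% to 95% in autistic children, while it "may reach 16.50% in children of the population". From this it draws the consequence that "our sample will be sufficient for the validation of the neurometric test, achieving a statistical power close to 1".

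The rest of the article describes the measurement of SMD as follows:

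- **Instrument.** Section 2.4 (data list and Table 1) and Section 3.5.4 assess SMD by the smartphone application alone.
- **Scale.** Sections 3.5.4.1 to 3.5.4.3 list amplitudes, latencies, habituation changes, percentages of trials, durations, sway and correlations. A typical entry is "Percent PPI: The percentage inhibition of the ASR amplitude due to the prepulse".
- **Reference.** No other sensory instrument is among the data collected. The Short Sensory Profile appears only in the Introduction, as a criticised earlier tool, and the Abstract states that "Current caregiver-reported SMD assessments lack validity in autistic populations".
- **Aims and analysis.** The five aims in the Introduction include comparing prepulse inhibition (PPI) and startle habituation (SH) profiles across groups, but not validation. Sections 3.6.1 and 3.6.2 plan mixed models and exploratory tests, with no analysis of agreement, sensitivity, specificity or discrimination.

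**The concern.** The stated power belongs to one question and is attached to another. A power for two proportions is the chance of declaring the groups different when a known proportion in each is SMD-positive. It presupposes that each child can be classified and that the classification is accurate. Whether the smartphone test measures SMD accurately is what a validation would have to establish, so the figure assumes the answer.

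SMD is the outcome of the third aim, one of the variables related to each other in the fourth, and the candidate mediator in the fifth. A published power near 1 for this measure could lead a reader to take a null PPI or SH result as near-conclusive, or to report a difference between diagnostic groups as a validated test. Neither is supported by what the article states.

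**Working it through.** **Inputs from Section 2.2.4.** Two-sided 5%, z = "1.96 (corresponding to a 95% confidence level"); power 80%, z = "0.84 (corresponding to 80% power"); malnutrition 0.57 and 0.37; SMD prevalence 0.815 (lower end of the cited range) and 0.165. Evaluable per group: 100 × 0.95 = 95.

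**1. The article's own figures.**

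- Main calculation: (1.96 + 0.84)² × (0.57×0.43 + 0.37×0.63) / 0.20² = 7.84 × 0.4782 / 0.04 = 93.7, so 94. This reproduces, and 94/0.95 = 99 is consistent with 100.
- SMD prevalence contrast at 95 per group: SE = √[(0.815×0.185 + 0.165×0.835)/95] = √(0.28855/95) = 0.0551. Then 0.65/0.0551 − 1.96 = 9.8, so power exceeds 0.999. With the pooled-variance formula, 8 per group already give 80% power.

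Power close to 1 is therefore correct for that contrast.

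**2. What the figure says about accuracy (illustrative assumption).** Suppose a cut-off existed, the true prevalences were 0.815 and 0.165, and sensitivity and specificity were equal. The test-positive proportion in autistic children is 0.815×Se + 0.185×(1−Sp), and in the others 0.165×Se + 0.835×(1−Sp). At 100 per group:

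| Se = Sp | Autistic | Others | Power |
|---|---|---|---|
| 0.8 | 0.689 | 0.299 | >0.999 |
| 0.7 | 0.626 | 0.366 | 0.96 |
| 0.6 | 0.563 | 0.433 | 0.45 |

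A test that misclassifies 30% of children would still separate the groups with 96% power, so high power here is not evidence of validity. The relevant quantity would be precision. With 100 reference-positive children and an observed sensitivity of 0.80, the 95% Wilson interval is 0.71 to 0.87.

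**3. What the design can do: compare a continuous measure between groups.** Assume one summary value per child, two-sided 5%, no multiplicity adjustment and a normal approximation.

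- Power at 95 vs 95 is Φ(d/√(2/95) − 1.96), with √(2/95) = 0.1451. It is 0.28 at d = 0.2, 0.54 at 0.3, 0.93 at 0.5, 0.985 at 0.6 and >0.99 at 0.8.
- Detectable d at 80% power: (1.96 + 0.8416) × 0.1451 = 0.41.
- 95 vs 190 (Groups B and C pooled, 200 × 0.95): 2.8016 × √(1/95 + 1/190) = 2.8016 × 0.1257 = 0.35.
- d for 99% power: (1.96 + 2.3263) × 0.1451 = 0.62. At 100 per group it is 0.61.

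**4. Correlation with CARS.** By Sections 2.4 and 3.5.2, CARS is scored in Group A only (Section 3.5.2.3 labels the autistic group B). With 95 children, the detectable r at 80% power is tanh(2.8016/√92) = tanh(0.292) = 0.28.

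**5. Sensitivity to usable recordings.** The 5% allowance covers non-response, while PPI and SH also need valid trials. If only 80 per group were usable (an assumption), detectable d would be 2.8016 × √(2/80) = 0.44 and r would be tanh(2.8016/√77) = 0.31.

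**The case against.** The strongest reply is that the sentence claims little. It is a secondary remark, limited to large effects, and the number reproduces. For a large continuous difference (d = 0.8) power is indeed above 0.99. If the cited prevalences are read as a threshold on a normal latent trait, 81.5% against 16.5% corresponds to d of about 0.90 + 0.97 = 1.87, so a continuous scale does not by itself defeat the claim. Clinician diagnosis defines the groups and CARS is scored, so known-groups validity could be examined with the data collected. The article is also condensed, and a classification rule could stand in a fuller document.

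Much of this stands. The arithmetic is not in error, and a known-groups comparison is possible. A reader might infer that the prevalence comparison cannot be run at all, but the text supports only that no rule for it is stated. What the reply does not rescue is the step to validation. The article gives no effect size for PPI or SH, so nothing ties the cited prevalences to the size of difference these measures will show, and the kind of validity is not named.

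Three further inferences are tempting and should not be drawn:

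- That "prevalent in 69–95% of autistic individuals" in the Abstract contradicts 81.5–95% in Section 2.2.4. The Introduction, which repeats the wider range, and Section 2.2.4 cite different sets of sources, one for individuals and the other for children.
- That the cited prevalences come from caregiver questionnaires. One reference is shared with the discussion of those tools in the Introduction, but the article does not say so.
- That SMD is the mediator throughout aims 3 to 5. Mediation belongs to aim 5 alone, and there it is exploratory.

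**Conclusion.** The concern holds as a misattributed power statement. Power above 0.999 is right for a two-proportion contrast of 81.5% against 16.5%. It is not the power or the precision of a validation, for which the article states no classification rule, reference measure, aim or analysis. For the available comparison by diagnosis, power is close to 1 only from d of about 0.6. At 80% power the detectable difference is about d = 0.41 (95 vs 95) or 0.35 (95 vs 190), and the detectable correlation with CARS in Group A is about r = 0.28.

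These figures rest on one summary value per child, 95 evaluable in Group A, two-sided 5% and no multiplicity adjustment. They would shift with the planned multilevel models on repeated trials, with the option of up to 150 children in Group A (Section 2.2.1), with the A:B ratio of about 1:2 in Section 2.3, or with loss of unusable recordings.

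A reader might infer that the study is undersized. The documents do not support that: the sample size is set by malnutrition prevalence and its calculation reproduces. This is a minor-to-moderate correction.

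**What to change.** In Section 2.2.4, delete the sentence about validation and power close to 1. Describe the SMD aim as group discrimination and feasibility, which matches the third aim and the feasibility assessment in Sections 4.2 and 4.3. Put in its place:

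> Assuming 95 evaluable children in each of two groups, one summary value per child, two-sided 5% and no multiplicity adjustment, the study has 80% power to detect a standardised difference of about d = 0.41 in a continuous PPI or habituation measure (about 0.35 if 95 are compared with 190 non-autistic children), and a correlation of about r = 0.28 with CARS within Group A.

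The cost is the rewording of two sentences and a less favourable figure. No participants, procedures or analyses are added.

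If validation is really intended, the article would instead have to name the type of validity, the reference measure and the cut-off, and justify the sample by precision or by an effect size on the PPI or SH scale. For validation against another sensory instrument, that means collecting a measure the study does not now list.
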